### Care-as-usual/restricted group

In the restricted group patients have to sleep in a supine position during the first 8 weeks. Hip flexion over 90 degrees and internal or external hip rotation more than 45 is not allowed for the first 8 weeks. Patient will be mobilized by the physiotherapist at the day of the operation or the first postoperative day with full weight bearing to tolerance.

### Experimental/reduced restricted group

In the reduced restricted group patients are allowed to sleep in any position they find comfortable. Hip flexion over 90 degrees and internal or external hip rotation more than 45 degrees is not allowed for the first 8 weeks. Patient will be mobilized by the physiotherapist on the day of the operation or the first postoperative day. Patient will be mobilized by the physiotherapist at the day of the operation or the first postoperative day with full weight bearing to tolerance.

Patients are instructed by the physiotherapist how to lie in bed and how to prevent more than 90 degrees of hip flexion and 45 degrees of rotation. Next to the general instructions as stated earlier, patients in this experimental group receive additional instructions on how to lie and turn in bed by preventing more than 90 degrees of hip flexion and 45 degrees of rotation.

### Main study parameters/endpoints

Primary outcome measure is the difference in dislocation rate, expressed as a percentage, within the first 8 weeks between the group that receives postoperative instructions with the advice to sleep in a supine position for the first 8 weeks postoperatively and the group that receives postoperative instructions without any restriction on sleeping position. The diagnosis of a dislocated hip will be confirmed by clinical examination and X-ray findings.

### Secondary study parameters/endpoints

Secondary outcome measures are patient’s compliance with postoperative instructions, the influence of sleeping position restrictions on quality of sleep [18], the influence of sleeping position restrictions on patient satisfaction (anchor questions rating the degree of perceived quality of sleep and burden of the restrictions prescribed, the Client Satisfaction Questionnaire) and the effects of the advice to sleep in a supine position for the first 8 weeks on functional recovery.

### Other study parameters

These parameters include:Resumption of specific activities following THA such as driving a car.The use of assistive devices (e.g. pillow between the legs during sleep, crutches).The self-reported compliance of patients with the restrictions prescribed.Satisfaction with received quality of care (Client Satisfaction Questionnaire).

### Study procedures

After inclusion and prior to surgery, subject patients will complete the baseline questionnaire at the outpatient clinic during the intake by the nurse practitioner. The physiotherapist will mobilize patients on the day of the operation or the first postoperative day. During this mobilization patients are instructed how turn in bed and how to prevent more than 90 degrees of hip flexion and 45 degrees of rotation. The only difference in instruction between the two study arms is the sleeping position. When discharged to home or nursing home, patients receive a booklet describing the instructions relevant to the study arm they are assigned to. This booklet serves as an enchiridion for partners, physiotherapists, and other persons involved in the care of the patient. In addition, patients are handed a standardized diary booklet in which they are asked to document their sleeping position, exercise activities, experience of pain and any further comments they may want to convey. Patient will visit the outpatient clinic preoperatively and then at 8 postoperative weeks. Routine physical examination will be performed by the orthopedic surgeon. All scores and measurements will be recorded by the nurse practitioner who will also collect the diary booklet from the patients. Preoperative functional assessment will be done by pain severity (Visual Analogue Scale: range 0–10), hip function (Hip Disability and Osteoarthritis Outcome Score) and quality of life (EQ-5D). At 8 weeks follow-up the same functional assessment will be recorded by the nurse practitioner. This visit is combined with the regular postoperative control by the orthopedic surgeon. At 6, 12 and 24 months there will be follow-up questionnaires by Email, paper or telephone depending upon the availability of the patients’ Email addresses. The primary outcome: dislocations within the first 8 weeks, will be recorded in the patient’s file when visiting the emergency department.

### Sample size calculation

The maximum allowable difference in proportion in which there is still equality in the effect is not known in the literature. Previous studies suggested “a threefold difference in dislocation rate” to be a clinically relevant difference [4]. Since the literature is suggesting an average dislocation rate of 2.03 % [8] in the posterolateral surgical approach, a dislocation percentage between 2.03 and 6.09 % is considered to be “equal.” Hence, the planned sample size is *n* = 456 THA patients. (One-sided, *α* = 0.025, *β* = 0.80, missing data 20 %).

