#### Primary analysis

Descriptive statistics were calculated for all variables. Depending on the type of data were compared between the groups using either a *t* test (continuous) or chi-square (categorical).

The intervention group that receives postoperative instructions without any restriction on sleeping position will be declared non-inferior to the group that receives postoperative instructions with the advice to sleep in a supine position for the first 8 weeks postoperatively in case it can be demonstrated that the difference between these 2 groups does not exceed “a 3-fold difference in dislocation rate” in favor of the supine sleeping position group. This margin corresponds to the definition of clinically relevant difference in dislocation rate by Peak et al.

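### The 80% power stated for 456 patients does not hold together with one-sided alpha 0.025: a test that keeps the alpha has about 66% power at the planned 380 evaluable patients

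*Protocol article*

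**What the plan says.** The section on sample size starts from a literature rate ("the literature is suggesting an average dislocation rate of 2.03" %) and sets the tolerance by a threefold rule: "a dislocation percentage between 2.03 and 6.09 % is considered to be “equal". From this it gives the number of patients and the settings behind it: "Hence, the planned sample size is *n* = 456 THA patients. (One-sided, *α* = 0.025, *β* = 0.80, missing data 20" %. The 0.80 labelled β can only sensibly be read as power. No formula is named.

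The Primary analysis section gives one general rule for comparing groups: "Depending on the type of data were compared between the groups using either a *t* test (continuous) or chi-square (categorical". It then states the non-inferiority criterion in words, as a threefold difference in dislocation rate. It names no test or interval for that decision. The primary endpoint, under Main study parameters/endpoints, is the difference between the arms in the percentage dislocating within 8 weeks.

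**The concern.** A one-sided alpha and a power describe one decision rule, so both must hold for the same test. The sample size matches a formula whose standard error assumes 2.03% in both arms. That is the variance when the arms are truly equal. It is not the variance at the non-inferiority boundary, where the experimental arm is at 6.09%. With many events the distinction is small; with about four per arm it is not.

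Two things are at stake. If the analysis used the matching Wald limit, a protocol with three times the dislocation rate would be accepted about 1.5 times as often as stated (3.8% against 2.5%). If the analysis used a test that keeps 2.5%, a truly equivalent protocol would fail about one time in three rather than one in five, and an inconclusive result would be judged against a power the design did not have.

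**Working it through.** **Inputs.** From the Sample size calculation section: rate 2.03% in both arms, upper bound 6.09%, so the margin is 6.09 − 2.03 = 4.06 points; one-sided alpha 0.025 (z = 1.960); power 0.80 (z = 0.842); 20% missing. Allocation 1:1 is assumed: it is not stated, but two arms and even block sizes fit it.

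**Reproducing 456.** Unpooled normal approximation:

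n per arm = (1.960 + 0.842)² × 2 × 0.0203 × 0.9797 / 0.0406² = 189.4, rounded up to 190.

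190 × 2 = 380 evaluable, and 380 × 1.2 = 456 exactly. Alternatives do not give 456. Before any allowance for missing data, a pooled comparison of 2.03% with 6.09% needs 370 per arm (418 with continuity correction), a log risk ratio 628 and a log odds ratio 654.

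**Expected events.** 190 × 0.0203 = 3.9 per arm.

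**Variance at the boundary.** The formula uses 2 × 0.0203 × 0.9797 = 0.0398. The restricted estimates under the non-inferiority null give 0.0624. With that variance:

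n per arm = (1.960 × √0.0624 + 0.842 × √0.0398)² / 0.0406² ≈ 262.

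The same formula gives an approximate power of 63.8% at 190 per arm.

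**Exact enumeration.** All pairs of binomial counts were summed. The false-positive rate is taken at 6.09% (experimental) versus 2.03% (control), and power at 2.03% in both arms.

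| Evaluable per arm | Wald: false-positive | Wald: power | Score: false-positive | Score: power |
|---|---|---|---|---|
| 182 (456 less 20%) | 3.5% | 77.6% | 1.9% | 62.2% |
| 190 (as planned) | 3.8% | 80.5% | 2.1% | 65.9% |
| 228 (nobody missing) | 3.6% | 85.6% | 2.0% | 75.3% |

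Over control rates of 0 to 6% at 190 per arm, the score test's error peaks at about 2.3% and the Wald rule's at about 5.5%. The exact unconditional test ordered by the score statistic also has 65.9% power at 190. The Newcombe interval has 67.6% power with 2.1% error.

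**What the gap means in counts.** This is the largest number of experimental dislocations that still passes at 190 per arm:

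| Control dislocations | Wald | Score |
|---|---|---|
| 0 | 3 | 2 |
| 1 | 4 | 2 |
| 2 | 4 | 3 |
| 4 | 5 | 4 |

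Results such as 3 versus 0 or 4 versus 1 would therefore pass one rule and fail the other.

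**The case against.** The strongest reply is that nothing has been miscalculated. The stated inputs give 456 by a conventional planning formula, and such a formula does not commit the trial to a Wald interval. The choice of interval is commonly left to an analysis plan, which is not shown here. This stands in part. A reader might infer that the trial will run at a 3.8% error rate, or that it would accept 3 versus 0. The documents do not support that, because no Wald analysis is named. Nor is 456 an arithmetic error.

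The reply does not rescue the stated pair. If an analysis plan names a score test, the power is overstated by about 14 points at 380 evaluable. If it names Wald, the alpha is exceeded.

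Three further points limit the size of the claim:

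- The 66% belongs to score-type tests at 190 per arm. Other tests holding 2.5% across control rates gave 58 to 68%.
- A reader might infer that no test with 2.5% error can reach 80%. That is too broad. Tests calibrated only at the 2.03% control rate gave 70 to 74% at 190 per arm, and a recalibrated Wald statistic reached 81.0% at 228. Such tests do not hold 2.5% at other control rates, and the true control rate is unknown.
- Dislocations are recorded at emergency visits, there is a routine 8-week visit, and missing values are to be imputed. The intention-to-treat count may therefore be nearer 228 per arm, where the score test falls about 5 points short rather than 14.

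**Conclusion.** The point holds as one about stated power, of moderate severity. On the protocol's own inputs, alpha 0.025 and 80% power are not met together by either natural test at the planned 380 evaluable patients: Wald gives 80.5% power with 3.8% error, and the score test gives 2.1% error with about 66% power. Score-test power stays below 80% throughout, at about 62% with 182 per arm and 75% with 228.

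This rests on 1:1 allocation, a true rate of 2.03% in both arms, and the 4.06-point margin on the difference scale. The endpoint definition and the sizing support that scale. The threefold wording in the Primary analysis section could also be read as a ratio; on that reading power at 190 per arm is lower still, about 31 to 39%. The use of the unpooled formula is inferred from the exact match, not stated. How the 20% was added and the labelling of 0.80 as β are separate matters and do not affect the conclusion.

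**What to change.** In the Sample size calculation section, keep n = 456 and restate the power for a test that holds its level on the difference scale: about 66% with 380 evaluable, about 62% with about 365 (456 × 0.8), and about 75% with all 456.

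In the Primary analysis section, base the non-inferiority decision on the upper 97.5% limit for the risk difference from the Farrington-Manning / Miettinen-Nurminen score method, or its exact unconditional version, rather than on a Wald limit. Fix this before outcome data are compared by arm: with about eight dislocations expected in total, a choice made afterwards could decide the result.

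The cost is one sentence and a corrected figure. The downside is a less favourable stated power and, compared with a Wald limit, a success threshold stricter by one or two experimental-arm events at the control counts tabulated above. Enrolment does not change.

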**Methods/Design:**

After providing informed consent a group of 456 patients with symptomatic coxarthrosis will be randomized to receive a THA either with care as usual, i.e. receiving postoperative restrictions including the advice to sleep in a supine position for the first 8 weeks postoperatively, or reduced restrictions with no recommendations regarding the position during sleeping. Primary outcome measure will be the percentage of early dislocations within the first 8 weeks after THA. Secondary outcome measures will be patient satisfaction, time to functional recovery, quality of sleep and patient’s self-reported compliance with postoperative instructions.

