## Methods/Design

### Study design

The study design is a single***-***center, parallel-group, stratified, randomized trial with a planned duration of 3 years in which 456 primary THA patients will be allocated to either a care-as-usual group receiving postoperative restrictions including the advice to sleep in a supine position for the first 8 weeks postoperatively or an experimental group, receiving postoperative instructions without restrictions on sleeping position after THA surgery. The experimental group does not use a pillow between the legs in any sleeping position and the care-as-usual group, that is only allowed to sleep in a supine position, is advised to use a pillow between the legs while doing so.

A non-inferiority design was chosen as a standard approach to assess similarity of results of the experimental as opposed to the care-as-usual treatment. In order to avoid an imbalance in treatment assignments and to reduce the opportunity for bias and confounders, a stratified blocked randomization technique will be applied with random sequences of varying block sizes (varying from *n* = 2, *n* = 4 or *n* = 6). Among the stratification factors are operating surgeon and the preferred self-reported sleeping position (supine, prone, on the side, combination/no clear preference) of the patient. Measurements will be taken at baseline (preoperatively), 8 weeks (at regular polyclinic visit) 6, 12 and 24 months after surgery (postoperatively).

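### The planned 456 patients keep 80% power with up to 16.7% missing data, not the stated 20%, and power is printed as β = 0.80 (minor arithmetic error)

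*Protocol article*

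**What the plan says.** The Sample size calculation section of the protocol article gives these inputs:

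- Control rate: "the literature is suggesting an average dislocation rate of 2.03" per cent.
- Equivalence range: "a dislocation percentage between 2.03 and 6.09 % is considered to be" equal, from a three-fold difference.
- Size: "Hence, the planned sample size is" 456 in total.
- Error rates and loss: one-sided α = 0.025, then β and the allowance for missing data as "0.80, missing data 20" per cent.

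The section prints neither the number needed before the allowance nor how the allowance was applied. The total is repeated in the Abstract ("a group of 456 patients with symptomatic coxarthrosis will be randomized") and under Study design, which also states the framework: "A non-inferiority design was chosen as a standard approach to assess similarity of results".

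**The concern.** A loss allowance of 20% means that 80% of those randomised are expected to be evaluable, so the required number has to be divided by 0.8. Multiplying by 1.2 is a common slip and gives too few. If 456 came from that slip, the size, the power and the missing-data allowance in the same sentence cannot all be true.

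The symbol is also wrong. β conventionally denotes the type II error, so β = 0.80 read literally describes a trial with 20% power.

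Readers will use these figures to judge an inconclusive or a non-inferior result. The allowance has real work to do, because the Populations section makes the per-protocol set one of the primary analyses and removes patients without 8-week and/or 6-month data or with sleeping-position compliance below 80%.

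**Working it through.** **Inputs.** From Sample size calculation: p = 0.0203, taken as the true rate in both arms; margin Δ = 0.0609 − 0.0203 = 0.0406; one-sided α = 0.025 (z = 1.960); 0.80 read as power (z = 0.8416); 20% missing. Allocation of 1:1 is an assumption. No ratio is printed, but two arms with "a stratified blocked randomization technique will be applied with random sequences of varying block sizes" of 2, 4 or 6 imply it.

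**Step 1: reproduce the plan's figure.** Unpooled non-inferiority formula for a difference in proportions:

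n per arm = (1.960 + 0.8416)² × 2 × 0.0203 × 0.9797 / 0.0406² = 189.4, so 190 per arm and 380 in total.

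380 × 1.2 = 456, the printed figure exactly.

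**Step 2: apply the 20% allowance correctly.** 380 / 0.8 = 475. In equal arms, 190 / 0.8 = 237.5, so 238 per arm and 476 in total. That is 19 or 20 patients more than 456, about 4%.

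**Step 3: what 456 delivers.** Power = Φ(0.0406 / √(2 × 0.0203 × 0.9797 / n) − 1.960), with n per arm:

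| Missing | Evaluable in total | n per arm | Power |
|---|---|---|---|
| 0% | 456 | 228 | 86.7% |
| 16.7% | 380 | 190 | 80.1% |
| 20% | 364.8 | 182.4 | 78.5% |

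The loss that 456 can absorb is 1 − 380/456 = 16.7%.

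**Step 4: could another route give 456?** None of the alternatives tried does, either before or after inflation by either rule. Totals before inflation:

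- Pooled test of 2.03% v 6.09%: 740, or 836 with continuity correction.
- Farrington-Manning: 524.
- Log risk ratio with a margin of 3: 1256.
- Unpooled formula with 90% power: 508.
- Unpooled formula with one-sided α = 0.05: 300, which becomes 375 (dividing by 0.8) or 360 (multiplying by 1.2).

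Rounding the inputs to 2% and 4 points gives 386, then 483 or 464.

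**Step 5: the β label.** Taking β = 0.80 literally changes the sign of the second z value: (1.960 − 0.8416)² × 0.039776 / 0.0016484 = 30.2, so 31 per arm and 62 in total. That is nowhere near 456. The calculation used 0.80 as power, and only the label is wrong.

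**The case against.** **The multiplication by 1.2 is not printed.** This is correct. The article condenses a fuller protocol, and the step is an inference from an exact match. The conclusion does not need it: 80% of 456 is 364.8, below the 380 required by the one formula found that leads to 456. Every other method tried at the same α and power requires more.

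**The shortfall may never arise.** The 20% is a planning allowance. Under Study procedures, dislocations are recorded in the patient's file at emergency visits and there is a routine visit at 8 weeks, so the primary outcome may lose fewer than 16.7%. Multiple imputation is also planned. This stands for the intention-to-treat analysis. It is weaker for the per-protocol analysis, which is also primary and could lose more. Either way, the sentence as printed claims cover for 20% and does not have it.

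**Stronger readings.** A reader might infer three things that the documents do not support:

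- *That the trial was planned with 20% power.* Step 5 rules this out.
- *That the mislabelled β contributes to the shortfall.* It does not; the shortfall comes from the allowance alone.
- *That true power is about 62%.* Exact binomial enumeration with a Farrington-Manning score limit gives about 62% at 182 per arm on an absolute 4.06-point margin. This reflects a different test, with about 182 × 0.0203 = 3.7 expected events per arm, and not the inflation step: at the correct 190 evaluable per arm it is still only about 66%. The Primary analysis section names no non-inferiority test or interval, and its three-fold margin can also be read as a ratio. The 62% is a fair separate caveat about the Wald planning formula, but it is not a figure that the sponsor should print as the trial's power.

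**Conclusion.** Wrong as written, and minor. The stated size, power and missing-data allowance do not fit together: 456 keeps 80% power with up to 16.7% missing and gives about 78.5% with 20% missing. The error amounts to about 1.5 power points, or 19 to 20 patients. The β entry is a separate labelling error in the same line.

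This rests on the unpooled formula, 2.03% in both arms, an absolute margin of 4.06 points and 1:1 allocation. The first three are supported by the exact reproduction of 456, and the last by the block sizes. It would be wrong to conclude that the design is materially underpowered because of this slip: with 380 evaluable patients the planning formula gives 80.1%.

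**What to change.** Restate the parenthesis in Sample size calculation along these lines: one-sided α = 0.025; power = 0.80 (β = 0.20); 380 evaluable patients required; 456 randomised allows for 16.7% missing data; with 20% missing, power is about 78.5%.

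The total of 456 in the Abstract and under Study design can stay. No extra patients and no change to design, margin or analysis are needed. The cost is a text correction that makes one stated figure slightly less favourable. Any comment on the Wald approximation at low event counts should be made separately and kept out of this correction.

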### Statistics

#### Populations

Primary analyses will be performed for both the intention-to-treat (ITT) and per-protocol (PP) populations. The PP population of patients will comprise those who completed all measurements and did not have any reasons for exclusion from this population, including no baseline data, no data at 8 weeks and/or 6 months or major protocol violations (e.g. position compliance < 80 %).

Additional analysis will be based on an ITT (All Patients Treated) population that consists of all randomized patients who had both a baseline and at least one post-baseline measurement.

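### The stated 80% power rests on 380 evaluable patients, which the primary per-protocol analysis does not keep under the plan's own exclusions

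*Protocol article*

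**What the plan says.** The protocol article, Sample size calculation, takes a rate of 2.03% ("the literature is suggesting an average dislocation rate of 2.03") and sets the limit of equivalence by "a dislocation percentage between 2.03 and 6.09 % is considered to be “equal". It then gives "456 THA patients" with the settings "One-sided, *α* = 0.025, *β* = 0.80, missing data 20" per cent. The printed β of 0.80 makes sense only as power. One allowance for loss is stated, and it is labelled as missing data.

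The Populations section then says: "Primary analyses will be performed for both the intention-to-treat (ITT) and per-protocol (PP) populations". Patients leave the PP set for lacking baseline data and for "no data at 8 weeks and/or 6 months or major protocol violations", with position compliance under 80% given as an example of such a violation. No expected rate of non-compliance appears anywhere in the article.

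The Missing data section imputes missing values for the ITT population. The Primary analysis section gives one non-inferiority criterion and does not say whether it must be met in both populations.

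**The concern.** One power figure is printed, and two analyses are called primary. The allowance behind that figure covers missing data. The PP set loses patients for missing data and for poor compliance, so it has a source of loss that the sample size did not count. Because missing values are imputed for ITT, the missing-data loss also falls mainly on PP.

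In a non-inferiority trial the PP analysis is the usual safeguard against a dilution of differences by non-adherence. If it fails to show non-inferiority, the reader needs to know whether the set was large enough to have succeeded. With a single 80% in print, readers would take that figure to apply to PP.

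**Working it through.** **Inputs.** From the Sample size calculation: rate 2.03%, taken as true in both arms; margin 6.09 − 2.03 = 4.06 percentage points; one-sided α 0.025; power 80%; missing data 20%; total 456. Allocation 1:1 is an assumption; the ratio is not printed, but all block sizes are even.

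**Step 1: reproduce 456.**
n per arm = (1.960 + 0.842)² × 2 × 0.0203 × 0.9797 / 0.0406² = 189.4, so 190 per arm and 380 in total. 380 × 1.2 = 456 exactly. Division by the retained fraction would give 380 / 0.8 = 475.

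**Step 2: loss that PP can bear.**
380 / 456 = 83.3%, so PP keeps 380 only if all exclusions together are at most 16.7%. The plan's missing-data figure alone is 20%.

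**Step 3: PP at 20% missing, no compliance exclusion.**
456 × 0.8 = 364.8, about 365, or 182 per arm.
Power = Φ(0.0406 / √[0.0203 × 0.9797 × (1/n_C + 1/n_E)] − 1.96).
With 182 in each arm the standard error is 0.01478, the ratio is 2.746, and power is Φ(0.786) = 78.4%. Exact binomial power of the same rule (Wald limit with unpooled variance) is 77.6%.

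**Step 4: add compliance exclusions in the control arm.** The rates are assumptions. The experimental arm stays at 182.

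| Controls excluded | n_C / n_E | Normal approximation | Exact |
|---|---|---|---|
| 0% | 182 / 182 | 78% | 78% |
| 10% | 164 / 182 | 76% | 80% |
| 20% | 146 / 182 | 74% | 78% |
| 30% | 127 / 182 | 70% | 76% |
| 40% | 109 / 182 | 66% | 69% |

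The exact column is not monotone. With about 2% events the counts are small, and the rule moves in steps, so differences of a point or two carry little meaning.

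**Step 5: ITT by the same formula.** If all 456 contribute (228 per arm), power is 87%. If 20% are missing and not recovered (182 per arm), it is 78%.

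**The case against.** The strongest reply is that sizing on one comparison with one attrition allowance is common, that an article condenses its protocol, and that the shortfall which can be shown without assumptions is about 2 points. That shortfall comes from the inflation formula and not from compliance. The last part stands, and the size of the claim must reflect it. The first part does not remove the point: the article itself prints the power, labels the allowance and names PP as primary, and these statements do not fit together.

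A reader might infer more than the documents support in five places:

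- **That every compliance exclusion lowers power.** By exact calculation it does not: 10% of controls excluded gives 80.0%, against 77.6% with none.
- **That PP power falls to 69% or 57%.** Those are the normal-approximation figures if 20% or 40% of both arms are excluded. The experimental group may sleep in any comfortable position, so a position criterion has little to exclude there.
- **That the protocol predicts poor compliance.** The Background and Discussion cite sleeping difficulties under restrictions in an earlier study. They do not report that patients broke the rule or fell below 80%. The Discussion treats compliance as something to be measured.
- **That both analyses must succeed.** No such rule is stated, so a joint power figure would rest on a decision rule that the plan does not contain.
- **That the 80% belongs to ITT.** Neither ITT case in Step 5 gives 80%.

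**Conclusion.** The point holds in a limited form. The 80% describes 380 evaluable patients, and the plan's own 20% missing data leaves PP with about 365 and about 78% power before any patient is removed for compliance. This first gap is small and is an inflation error. Compliance exclusions generally lower power further. If they fall on controls only, the loss is modest up to about 20–30% of controls and material beyond that, with 66% (normal approximation) or 69% (exact) at 40%.

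The result assumes a true rate of 2.03% in both arms, 1:1 allocation, and exclusions unrelated to outcome. The compliance rates are assumed, so the documents do not fix the size of the loss. If all PP exclusions together stay at or below 16.7%, the stated power is kept, but that is less than the plan allows for missing data alone.

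**What to change.** In the Sample size calculation, state that 80% refers to 380 evaluable patients and does not hold for PP under the plan's own exclusions. Give PP power at 456 as about 78% with 20% missing and no compliance exclusion, followed by its values over a stated range of control-arm exclusions, for example 10% to 40%, marked as assumptions. Do not assign 80% to ITT; if an ITT figure is given, state about 78% (missing patients not recovered) to 87% (all 456 contributing). Report joint power only if the plan is changed to require success in both populations.

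The cost is a sentence or two and a less favourable printed figure. The number of patients, the analyses and the margin stay as they are.

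### The per-protocol set, one of two primary populations, ties an 8-week endpoint to data collected months later and excludes on an undefined compliance rule that probably affects mainly controls

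*Protocol article*

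**What the plan says.** All references are to the protocol article.

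- **Endpoint** (Main study parameters/endpoints): "Primary outcome measure is the difference in dislocation rate, expressed as a percentage, within the first 8 weeks". Under Study procedures, dislocations "will be recorded in the patient’s file when visiting the emergency department".
- **Primary populations** (Populations): "Primary analyses will be performed for both the intention-to-treat (ITT) and per-protocol (PP) populations".
- **Entry to PP** (same section): "The PP population of patients will comprise those who completed all measurements". Listed reasons for exclusion are "no baseline data, no data at 8 weeks and/or 6 months or major protocol violations (e.g. position compliance" below 80%).
- **Measurement schedule** (Study design): "Measurements will be taken at baseline (preoperatively), 8 weeks (at regular polyclinic visit) 6, 12 and 24 months after surgery".
- **Sleeping rule, control arm**: "In the restricted group patients have to sleep in a supine position during the first 8 weeks".
- **Sleeping rule, experimental arm**: "In the reduced restricted group patients are allowed to sleep in any position they find comfortable".

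Study procedures names sleeping position as the sole difference in instruction between the arms. The Discussion says that compliance with the sleeping-position instructions will be studied in relation to preferred position, which is also a stratification factor. The Interventions section, however, lists supine-only sleep with a pillow among the guidelines given to all patients.

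**The concern.** Two stated rules select the PP set on what happens after randomisation.

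**Later data decide who counts for an early endpoint.** Dislocation status is settled at 8 weeks and does not come from the later questionnaires. A patient with an X-ray-confirmed dislocation in week 3 who returns no 6-month form still leaves PP, and the event leaves too. This applies to both arms. Patients with an early complication could plausibly be the ones who stop returning forms.

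**The one named protocol violation is undefined and probably lopsided.** A threshold on position compliance bites where a position is prescribed, and that is the control arm. PP would then set controls who managed to sleep supine against a largely unselected experimental arm. Preferred sleeping position, on which randomisation was stratified, is an obvious candidate to differ between those groups.

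In a non-inferiority trial the PP result is meant to check the intention-to-treat result. A PP set that can drop events, or that selects one arm, is a poor check.

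**Working it through.** **Inputs from the document.** Control rate 2.03% and upper limit 6.09%, so an absolute margin of 6.09 − 2.03 = 4.06 points; one-sided α 0.025; power 0.80 (printed as β); 20% missing; total 456 (Sample size calculation). Equal allocation is assumed, giving 228 per arm.

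**Reproducing the plan's figure.** n per arm = 2 × 0.0203 × 0.9797 × (1.960 + 0.842)² / 0.0406² = 189.4, rounded up to 190. Total 380, and 380 × 1.2 = 456. So the plan's number follows from a normal approximation with unpooled variance on the absolute scale, and the same formula is used below. After 20% loss, 228 × 0.8 = 182 per arm.

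**Effect of the later-data rule (drop-out shares assumed).** Suppose a share q of dislocators in each arm misses a later measurement. The PP risk is then p(1 − q)/(1 − pq). Take true risks exactly at the margin, 6.09% and 2.03%, with 182 per arm. P(declare non-inferiority) = Φ((0.0406 − difference)/SE − 1.96).

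| q | PP risk, experimental | PP risk, control | Difference | SE | P(false non-inferiority) |
|---|---|---|---|---|---|
| 0 | 6.09% | 2.03% | 4.06 points | 2.06 points | 2.5% |
| 20% | 4.93% | 1.63% | 3.30 points | 1.86 points | 6% |
| 40% | 3.75% | 1.23% | 2.52 points | 1.63 points | 16% |

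For q = 20%: 0.0609 × 0.8/(1 − 0.0122) = 0.0493, 0.0203 × 0.8/(1 − 0.0041) = 0.0163, and Φ(0.0076/0.0186 − 1.96) = 0.06.

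This shrinkage belongs to the absolute scale. The ratio of the two PP risks stays near 3 (4.93/1.63 = 3.02).

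**Effect of the compliance rule on power (non-compliance assumed).** Power = Φ(0.0406/√(0.0203 × 0.9797 × (1/182 + 1/n₀)) − 1.96), with n₀ the controls left after 20% missing in both arms.

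| Controls excluded | n₀ | Power |
|---|---|---|
| 0% | 182 | 78% |
| 20% | 146 | 74% |
| 30% | 128 | 70% |
| 50% | 91 | 61% |

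With no missing data (228 per arm), power is 87% without exclusions and 83%, 80% and 71% at the same three exclusion rates.

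**Effect of the compliance rule on bias (relative risks assumed).** Let both arms have a true risk of 2.03% and exclude 30% of controls. If non-compliers carry r times the compliers' risk, PP control risk = 0.0203/(0.7 + 0.3r).

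- r = 2: 1.56%, a spurious +0.47 points against the experimental arm.
- r = 3: 1.27%, a spurious +0.76 points.
- r = 0.5: 2.39%, a spurious −0.36 points in its favour.

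The sign depends on r, about which the document says nothing.

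**The case against.** **Intention-to-treat is also primary.** This stands. An event dropped from PP remains in the patient's file and in the intention-to-treat analysis, and the Missing data section compares the pooled imputed result with the PP result. The defect weakens one of two primary analyses and does not remove the other. Imputation does not restore a dropped patient to PP.

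**The compliance rule may not be one-sided.** This stands in part. The threshold is given only as an example and is not defined. The experimental arm also has bed-related instructions: no pillow between the legs, and lying and turning within limits of flexion and rotation. The Interventions list even prescribes supine sleep for everyone. A reader might infer that only controls can fail the rule. The text makes that probable, through the two arm descriptions, Study procedures and the Discussion, but does not settle it. Nor should the later-data rule be described as acting in one arm, because it applies to both.

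**A single lost event need not reverse the result.** This stands. A reader might infer a flip from Newcombe upper limits at 182 per arm: 5 against 4 dislocations gives 4.32 points (above 4.06) and 4 against 4 gives 3.58. But the document names no interval method, and with the unpooled variance behind its own sample size the limit for 5 against 4 is 3.74 points, which passes. With 146 controls, 5 against 4 gives 3.90 by Newcombe and also passes. So few events make any analysis fragile, and that is not specific to this rule.

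**The rates are assumed.** True: the document gives no non-compliance or drop-out figures. At 20% non-compliance the power loss is modest. The case against the later-data rule does not rest on these rates, because the rule removes known outcomes whatever their number.

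**Details may be in a fuller document.** The PP rules criticised here are stated in the article and are wrong for this endpoint as they stand.

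**Conclusion.** Wrong as written, and it should be fixed. For dislocation within 8 weeks, requiring completed measurements or 6-month data has no purpose and can discard confirmed events in both arms. Even on the narrowest reading, where only the 8-week and 6-month exclusions apply, the window runs well past the endpoint. On the absolute scale used for the sample size, the illustrated loss of 20% to 40% of dislocators raises false non-inferiority in PP from 2.5% to about 6% to 16%. This assumes equal loss shares in both arms and 182 analysed per arm.

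The compliance criterion is undefined and probably excludes mainly or only controls. The bias has no known sign, and power is about 74%, 70% or 61% rather than 78% under assumed exclusions of 20%, 30% or 50% on top of 20% missing.

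A reader might go further and conclude that the trial's primary conclusion is unreliable or that the benefit of stratification is lost. The document does not support this: intention-to-treat is primary and keeps the events, and surgeon and preferred sleeping position remain available for adjustment.

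**What to change.** 1. For the dislocation endpoint, define PP by eligibility, assigned instructions received, and known dislocation status at 8 weeks.
2. Delete the completed-measurements and 6-month requirements for this endpoint. Keep them only for the questionnaire endpoints.
3. Define position compliance separately for each arm, and assess it only up to the earlier of dislocation or 8 weeks.
4. Reconcile the Interventions list, which gives supine-only sleep to all patients, with the experimental-arm description and Study procedures.
5. Because the compliance exclusion is probably one-sided, add a sensitivity analysis that reports the PP result without it, or adjusted for the recorded stratification factors. Such adjustment would not remove selection on unrecorded factors.

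The cost is revised wording and a little extra analysis. No new data are needed, and the intention-to-treat analysis is unchanged.
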